## Abstract

**Background:**

Endovenous thermal techniques, such as endovenous laser ablation (EVLA), are the recommended treatment for truncal varicose veins. However, a disadvantage of thermal techniques is that it requires the administration of tumescent anaesthesia, which can be uncomfortable. Non-thermal, non-tumescent techniques, such as mechanochemical ablation (MOCA) have potential benefits. MOCA combines physical damage to endothelium using a rotating wire, with the infusion of a liquid sclerosant. Preliminary experiences with MOCA showed good results and less post-procedural pain.

**Methods/Design:**

The Laser Ablation versus Mechanochemical Ablation (LAMA) trial is a single-centre randomised controlled trial in which 140 patients will be randomly allocated to EVLA or MOCA. All patients with primary truncal superficial venous insufficiency (SVI) who meet the eligibility criteria will be invited to participate in this trial. The primary outcomes are intra-procedural pain and technical efficacy at 1 year, defined as complete occlusion of target vein segment and assessed using duplex ultrasound. Secondary outcomes are post-procedural pain, analgesia use, procedure time, clinical severity, generic and disease-specific quality of life, bruising, complications, satisfaction, cosmesis, time taken to return to daily activities and/or work, and cost-effectiveness analysis following EVLA or MOCA. Both groups will be evaluated on an intention-to-treat basis.

**Discussion:**

The aim of the LAMA trial is to establish whether MOCA is superior to the current first-line treatment, EVLA. The two main hypotheses are that MOCA may cause less initial pain and disability allowing a more acceptable treatment with an enhanced recovery. The second hypothesis is that this may come at a cost of decreased efficacy, which may lead to increased recurrence and affect longer term quality of life, increasing the requirement for secondary procedures.

**Trial registration:**

ClinicalTrials.gov identifier: NCT02627846, registered 8 December 2015

EudraCT number: 2015-000730-30

REC ref: 15/YH/0207

R&D ref: R1788

## Background

Varicose veins are a common disease worldwide, and in the United Kingdom, it affects approximately one-third of the population [1]. They are associated with symptoms causing pain and disability, soft tissue damage and venous ulcer, resulting in significant quality of life impairments [2] with consequent healthcare costs [3].

Endovenous thermal ablation (EVTA) techniques, such as endovenous laser ablation (EVLA), are now widely accepted and they are recognised as the first-line treatment for truncal varicose veins or superficial venous insufficiency (SVI) [4, 5]. This approach has been shown to allow an enhanced recovery, with less pain and disability, resulting in superior early quality of life (QoL) when compared with surgical ligation and stripping, and improved efficacy when compared with foam sclerotherapy [6–11]. However, thermal ablation techniques carry the risk of damaging perivenous soft tissue and/or nerves. Thus, patients are treated with tumescent anaesthesia (TA), which requires multiple injections in order to infiltrate around the entire length of the target vein. Our Public and Patient Involvement (PPI) group and patients report that one of the major burdens associated with endovenous thermal ablation is the discomfort during injections of TA. Some patients still experience weeks of post-procedural pain despite the use of TA [12].

Mechanochemical ablation (MOCA), using the ClariVein^®^ device (Vascular Insights, Madison, CT, United States) is a newer treatment aiming to match the efficacy of thermal ablation whilst using a gentle sclerotherapy technique, with no requirement for TA. A catheter placed within the vein deploys a rotating hollow wire which causes physical damage to the endothelium and the vein goes into spasm. At the same time, a sclerosing agent is injected through the hollow wire into the vein, which results in protein denaturation, endothelial destruction and endoluminal fibrosis [13, 14]. Since no heat is involved and TA is made redundant, thermal-related complications such as pain, haematoma, induration and nerve injury could be reduced.

In the first human safety study, 30 great saphenous veins (GSVs) with primary SVI in 29 patients were treated with MOCA using sodium tetradecyl sulphate (STS) (Sotradecol). At 6 months [15] and at 2 years [16], the technical efficacy was 97 % (29 of 30) and 96 % (27 of 28), respectively. Several early case series have reported technical efficacy, with occlusion rates varying from 87 to 97 % [17–20]. There were no serious adverse events such as pulmonary embolism (PE), deep vein thrombosis (DVT) or nerve injury observed in all previous studies. Furthermore, prospective observational cohort studies suggest MOCA was associated with significantly less procedure times, lower post-procedural pain and faster recovery than endovenous thermal ablation techniques [21, 22]. To date, no studies have been performed to compare MOCA with EVLA in the treatment of SVI. The current study has been designed to compare MOCA with EVLA in the treatment of SVI in a randomised controlled trial (RCT).

## Methods/Design

### Study objectives

The aim of this randomised clinical trial is to establish whether MOCA is superior to the current first-line treatment, such as EVLA. The two main hypotheses are that MOCA may cause less initial pain and disability, allowing a more acceptable treatment with an enhanced recovery. The second hypothesis is that this may come at a cost of decreased efficacy, which may lead to increased recurrence and affect longer term quality of life, increasing the requirement of secondary procedures.

### Study design and setting

This is a phase IV randomised clinical trial in the setting of a University Teaching Hospital, based in United Kingdom, offering tertiary vascular surgery services.

### Inclusion criteria

The inclusion criteria are: aged 18 or over; primary symptomatic SVI; reflux greater than 0.5 seconds in the saphenous veins; clinical grades C2 to C6; proposed treatment lengths of at least 10 cm; treatment with either EVLA or MOCA is technically feasible; and written informed consent.

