During MOCA, the ClariVein^®^ catheter (Vascular Insights, Glasgow, UK) will be inserted, aided by the 0.018” guidewire, and its tip is placed near the SFJ and SPJ, as appropriate under DUS. The catheter is connected to a 9 V battery-motorised handle unit that controls wire rotation, and the patient is treated in a horizontal position. The wire is activated for 10 seconds in order to induce vasospasm, and the device is withdrawn with a speed of approximately 7 seconds per centimetre, while the sclerosant is continuously injected. The sclerosing agent will be sodium tetradecyl sulphate (STS), also known as STD injection and marketed as Fibrovein 3 %, 1 %, 0.5 % and 0.2 % Solution for Injection (STD Pharmaceutical Products, Hereford, UK). The concentration used will be 1.5 %, made from 2 ml ampoule of 3 % STS with equal measures of 2 ml sterile water (water for injection). Alternatively, diluting with 2 ml of 0.9 % normal saline is also satisfactory. The concentration and volume used will be clearly documented.

If required, concomitant ambulatory phlebectomy of the varicose tributaries will then be performed using the standard Oesch hook technique through 1–2 mm stab incisions. The same TA will be infiltrated around any tributaries to be treated. The phlebectomy sites will be dressed with Steri-Strip™ (3 M, St Paul, MN, USA), cotton wool, gauze and elastic compression dressings applied from foot to knee or groin, as appropriate. This will be exchanged for a thigh-length anti-thromboembolism stocking for 6 days after 24 hours. Patients will be advised to immediately mobilise within their comfort level, and to return to their normal activities and work as soon as they feel able to. Analgesia will not be routinely prescribed.

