### Sample size calculation

The power calculation is based upon the joint primary endpoints with 90 % power and 5 % significance. A published comparison of MOCA and radiofrequency thermal ablation found a reduction in intra-procedural pain from 35 mm to 19 mm on a 100-mm visual analogue scale (VAS) with a standard deviation of 20 mm [35]. This gives a required sample size of 33 patients per group or 73 in the trial including 10 % loss to follow-up. This difference is comparable with differences in patient-reported pain VAS, which was previously found to be associated with a difference in physical domains of quality of life and associated with changes in recovery time [8], and therefore can be judged to be clinically significant. Previous comparisons of radiofrequency ablation (RFA) with EVLA have suggested that EVLA is associated with more post-procedural pain [12, 36–38]. However older laser delivery technology (bare-tip fibres), shorter wavelength of laser (810–980 nm), additional treatment to truncal varicose vein with the allocated treatment at the same sitting, and general anaesthesia (GA) were involved; thus their findings may not be applicable today. Furthermore, no study has shown any significant benefit in quality of life relating to the reported differences.

The same study [35] reported complete target vein occlusion in 83 % of patients following MOCA at 1 month. Our previous RCT found target vein occlusion in 99 % at 1 year following EVLA [7]. A difference of this magnitude is likely to be clinically significant and have implications towards the long-term durability of the procedure, affecting effectiveness and cost-effectiveness. The required sample size to detect such a difference, if it exists, would be 62 per group or 137 including 10 % loss to follow-up. Taking this into consideration, the target sample size is 140.

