### Statistical analysis

Results will be evaluated based on an intention-to-treat analysis. Continuous data will first be tested for normality. Normally distributed data will be presented as mean and standard deviation, and hypothesis testing performed with paired and unpaired *t* tests, using two-sided significance tests with a 5 % significance threshold. If the data is not normally distributed, median and interquartile range values will be presented, with analysis using the Mann-Whitney *U* test for unrelated samples and Wilcoxon signed rank test for paired data. Categorical data will be analysed by means of *X*^2^ test or, if necessary, Fisher’s exact test. Occlusion rates will be presented as Kaplan-Meier curves, including censoring.

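### Adjusting the primary pain comparison for proposed treatment length, which is settled before randomisation, would be a modest and nearly free gain in precision

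*Protocol article*

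**What the plan says.** Under Inclusion criteria, one entry condition is "proposed treatment lengths of at least 10 cm", with no upper limit. Recruitment places a detailed duplex scan at the screening appointment where eligibility is decided, and Study visits puts baseline measurement before randomisation. A proposed length must therefore be judged before the arm is known.

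The article links length to how much is done in each arm. For thermal ablation, Background describes tumescent anaesthesia as a step "which requires multiple injections in order to infiltrate around the entire length of the target vein", and reports that patients find these injections a major source of discomfort. For MOCA, Treatment states that "the device is withdrawn with a speed of approximately 7 seconds per centimetre".

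Statistical analysis fixes the between-arm method for every continuous outcome: "Normally distributed data will be presented as mean and standard deviation, and hypothesis testing performed with paired and unpaired" t tests, or the Mann-Whitney test between arms if the data are not normal. No covariate is named, and Randomisation names no stratification factor. The only length that the article says will be recorded is the length actually treated, under Treatment.

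**The concern.** Intra-procedural pain has no baseline score, so the usual adjustment for a baseline value is unavailable. Proposed length is a natural substitute: it is fixed before allocation, it can vary widely above 10 cm, and more length means more tumescent infiltration in one arm and a longer withdrawal in the other. At 7 seconds per centimetre, withdrawal takes 7 × 10 = 70 s for 10 cm and 7 × 40 = 280 s for an illustrative 40 cm.

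If length predicts pain within arms, an unadjusted comparison leaves that variation in the error term and gives a wider confidence interval than the same patients could provide. The estimate matters as well as the test, because the trial intends to weigh any pain advantage of MOCA against a possible loss of efficacy.

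**Working it through.** **Inputs.** From Sample size calculation: pain 35 mm against 19 mm, a difference of 16 mm, "with a standard deviation of 20 mm"; 90% power and 5% significance; target 140. From Statistical analysis: "using two-sided significance tests with a 5 % significance threshold". From Fig. 1: 70 per arm. Pain during the procedure is recorded at the treatment visit (Table 1), so 70 per arm is a better basis than a figure reduced for loss to follow-up. The within-arm correlation r of proposed length with pain is not in the document and is an assumption throughout.

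**Step 1: reproduce the plan's own figures.**
- Pain: n = 2(1.960 + 1.282)² × 20² / 16² = 32.8, so 33 per group; 66 × 1.10 = 72.6, so 73. Both match.
- Occlusion, 83% against 99%: n = (1.960 + 1.282)² × (0.83 × 0.17 + 0.99 × 0.01) / 0.16² = 61.98, so 62 per group; 124 × 1.10 = 136.4, so 137. Both match.

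Occlusion therefore sets the trial size, and pain has about twice the patients it needs.

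**Step 2: the unadjusted pain comparison.** SE = 20 × √(2/70) = 3.38 mm; half-width = 1.96 × 3.38 = 6.63 mm. Power for 16 mm is 99.7% with 70 per arm, and 99.4% with 63 per arm if 10% were lost.

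**Step 3: adjust for length.** Residual SD = 20 × √(1 − r²); half-width = 1.96 × residual SD × √(2/70).

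| Assumed r | Residual SD (mm) | Half-width (mm) | Narrower by |
|---|---|---|---|
| 0 | 20.00 | 6.63 | 0% |
| 0.1 | 19.90 | 6.59 | 0.5% |
| 0.2 | 19.60 | 6.49 | 2.0% |
| 0.3 | 19.08 | 6.32 | 4.6% |
| 0.4 | 18.33 | 6.07 | 8.3% |
| 0.5 | 17.32 | 5.74 | 13.4% |
| 0.6 | 16.00 | 5.30 | 20.0% |

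**Step 4: power.** At 16 mm the gain is under 1 percentage point at any r. For an assumed smaller true difference of 10 mm with 70 per arm, power is 84.1% unadjusted, 87.3% at r = 0.3 and 92.7% at r = 0.5.

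**Step 5: chance imbalance.** The standardised difference in mean length between arms has standard deviation √(2/70) = 0.17. At r = 0.3 a one-standard-deviation imbalance moves the unadjusted pain estimate by 0.3 × 20 × 0.17 ≈ 1 mm. The 3.38 mm standard error already includes this variation.

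**The case against.** The strongest reply is that nothing here is a mistake. Allocation is by simple equal randomisation with no stated stratification, so an unadjusted two-sample comparison is valid. That stands. The choice of covariates may also be made in an analysis plan that is not shown, although the article as written does name unadjusted tests.

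The next reply is that the link between length and pain is assumed. This also stands. The article ties length to the extent of both procedures, but it ties discomfort only to the tumescent injections used for laser ablation. A withdrawal speed is not evidence of pain under MOCA, and phlebectomy under tumescent anaesthesia, possible in either arm, adds pain unrelated to truncal length. A reader might infer that length drives pain in both arms and that precision is certainly being lost; the document does not show that.

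A reader might also infer that chance imbalance in length leaves the pain result biased. It does not: random imbalance is covered by the unadjusted standard error. Nor could adjustment shrink the trial, because occlusion, not pain, sets the 140.

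Finally, adjustment is not wholly free. Trial status reports 75 of 140 patients (54%) already randomised by the end of December 2015, and the article does not say that a proposed length in centimetres is recorded. This is a real but manageable cost.

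What survives is that a pre-randomisation variable, plausibly prognostic by the article's own description, goes unused in a primary comparison and could be added at little cost.

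**Conclusion.** The point holds as an optional efficiency improvement. The planned pain test is valid and its power for the 16 mm difference exceeds 99%, so the trial's pain conclusion is not at risk at the design difference. The benefit is a tighter estimate: about 2%, 5% or 8% off the interval width at r = 0.2, 0.3 or 0.4, and essentially nothing if r is near zero. Power would gain noticeably only if the true difference were well below 16 mm. That is possible, since the 16 mm comes from a comparison with radiofrequency ablation rather than laser, but the 10 mm used above is an illustration and not a figure from the document. The sizes rest on SD 20 mm, 70 analysed per arm and an assumed r. The stronger reading, that the unadjusted analysis is wrong or demonstrably wasteful, is not supported.

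**What to change.** Before any outcome data are analysed, pre-specify:

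1. **Primary estimate.** The mean difference in intra-procedural pain from a linear regression of pain on arm and proposed treatment length in centimetres, with its 95% confidence interval.
2. **Sensitivity analysis.** The unadjusted comparison already planned, including the Mann-Whitney test if the data are not normal.
3. **Source of the covariate.** Proposed length from the screening duplex record made before allocation. The treated length documented at the procedure should not be used, because it is determined after allocation by a team that knows the arm.
4. **Missing values.** A simple rule fixed in advance, for example mean imputation with a missing-value indicator.

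The cost is one degree of freedom, a short change to the analysis text, one number on the case report form for new patients, and extraction from existing scan records for those already randomised. No extra patients or visits are needed.

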### Exclusion criteria

The exclusion criteria are: one of the treatments is thought to be preferable by either the patient or an experienced endovenous specialist; known allergy to medications or dressings used in the treatment; known right to left circulatory shunt; evidence of acute deep vein thrombosis or complete ipsilateral occlusion; pelvic vein insufficiency; active or recent thrombophlebitis (within 6 weeks); impalpable foot pulses with the Ankle Brachial Pressure Index of less than 0.8; pregnancy or breast feeding; active malignancy; immobility; involvement in other Clinical Trials of an Investigational Medicinal Product (CTIMP) within the last 6 months; and unwell or inability to comply with the requirements for follow-up visits.

### Treatment

All varicose vein procedures were carried out under ultrasound guidance and local anaesthesia (LA) by vascular surgeons who were experienced in both techniques of endovenous ablation. No preoperative analgesia or sedation is used. Initial vein access was performed under ultrasound guidance after injection of local anaesthetic (1 % lidocaine). With the patient in the reverse Trendelenburg position, the target vein will be cannulated percutaneously under duplex ultrasound scan (DUS) at the lowest point of demonstrable reflux using a 5-Fr sheath and dilator, followed by a 0.018” guidewire. The total length of truncal vein treated will be documented.

For EVLA, the dilator and guidewire will be exchanged for a larger 0.035” wire using the Seldinger technique. The treatment sheath is then introduced and its tip accurately positioned at the saphenofemoral junction (SFJ) or saphenopopliteal junction (SPJ) (as appropriate) under DUS, aiming for a flush occlusion. The patient is then put placed in the horizontal position, and perivenous tumescent anaesthesia (TA) is infiltrated around the entire length of the target vein under DUS using a spinal needle and a pedal-operated peristaltic pump. The constituents of TA are 100 ml of 1 % lidocaine with 1:200,000 epinephrine in 900 ml of 0.9 % sodium chloride, which is buffered to pH 7.4 with 10 ml of 8.4 % sodium bicarbonate. A sterile NeverTouch Gold-Tip laser fibre is introduced and locks with the treatment sheath. Endovenous laser energy is delivered using the VenaCure 1470 nm laser generator (Angiodynamics, Waterlooville, UK) set at a continuous power delivery of 10 W.

During MOCA, the ClariVein^®^ catheter (Vascular Insights, Glasgow, UK) will be inserted, aided by the 0.018” guidewire, and its tip is placed near the SFJ and SPJ, as appropriate under DUS. The catheter is connected to a 9 V battery-motorised handle unit that controls wire rotation, and the patient is treated in a horizontal position. The wire is activated for 10 seconds in order to induce vasospasm, and the device is withdrawn with a speed of approximately 7 seconds per centimetre, while the sclerosant is continuously injected. The sclerosing agent will be sodium tetradecyl sulphate (STS), also known as STD injection and marketed as Fibrovein 3 %, 1 %, 0.5 % and 0.2 % Solution for Injection (STD Pharmaceutical Products, Hereford, UK). The concentration used will be 1.5 %, made from 2 ml ampoule of 3 % STS with equal measures of 2 ml sterile water (water for injection). Alternatively, diluting with 2 ml of 0.9 % normal saline is also satisfactory. The concentration and volume used will be clearly documented.

If required, concomitant ambulatory phlebectomy of the varicose tributaries will then be performed using the standard Oesch hook technique through 1–2 mm stab incisions. The same TA will be infiltrated around any tributaries to be treated. The phlebectomy sites will be dressed with Steri-Strip™ (3 M, St Paul, MN, USA), cotton wool, gauze and elastic compression dressings applied from foot to knee or groin, as appropriate. This will be exchanged for a thigh-length anti-thromboembolism stocking for 6 days after 24 hours. Patients will be advised to immediately mobilise within their comfort level, and to return to their normal activities and work as soon as they feel able to. Analgesia will not be routinely prescribed.

### Primary outcomes

The joint primary outcomes will assess the hypothesised advantages and disadvantages of MOCA when compared with EVLA. The first will be patient-reported intra-procedural pain measured on a standardised 100-mm visual analogue scale (VAS). The second will be technical efficacy at 1 year, with successful procedure defined as complete occlusion of the target vein segment. This will be assessed using duplex ultrasound.

### Secondary outcomes

The secondary outcomes are procedure time, post-procedural pain, analgesia use, clinical severity, generic and disease-specific quality of life (QoL), bruising, complications, satisfaction, cosmesis, time taken to return to daily activities and/or work, and cost-effectiveness analysis following EVLA or MOCA.

The procedural time is from time of starting preparation to time of finishing dressing. Post-procedural pain will be recorded on a 100-mm VAS during the first week after treatment. The type and daily dosage of any analgesia taken by patients will also be recorded in a diary for the first week. Bruising, satisfaction with treatment and cosmesis will be recorded on a separate 100-mm VAS.

Major complications include deep vein thrombosis, pulmonary embolus, stroke, loss of vision, damage to major artery, vein and/or motor nerve. Minor complications include superficial thrombophlebitis, numbness, ecchymosis, persistent tenderness, lumpiness, skin staining and wound infection.

Disease-specific QoL is evaluated using the Aberdeen Varicose Vein Questionnaire (AVVQ), the Chronic Venous disease quality of life Questionnaire (CIVIQ-20) and the VEnous INsufficiency Epidemiological and Economic Study to evaluate Quality of Life and Symptoms (VEINES-QOL/Sym). AVVQ is a validated instrument that reflects the health status impairment associated specifically with venous disease [23]. CIVIQ-20 was developed more recently and it is designed to be more patient-centred [24]. VEINES-QOL/Sym is a 26-item patient-reported disease-specific questionnaire to evaluate the QoL and symptoms across the full spectrum of conditions related to chronic venous disorders of the leg [25].

Generic QoL is assessed using the Short Form 36-item (SF-36) and EuroQol 5-domain utility index (EQ5D). The SF-36 is a multidimensional measurement of general health, which yields eight domains of functional health and well-being scores [26–28]. EQ5D is an index scale mapping three available responses to five domain questions [29], which is transformed using the UK time trade-off tariffs into a global single index scale [30]. Both have undergone extensive testing of validity and reliability, including in the context of venous insufficiency and treatment [31–33].

Two validated objective measures will be used to assess and classify the severity of disease. The first is the Clinical severity, Etiology, Anatomy and Pathophysiology (CEAP) classification, which classifies severity into six grades. The second is the Venous Clinical Severity Score (VCSS), which grades three components from 0–3 with increasing severity, and then summates them into a single score. Clinical success is the objective improvement of clinical outcome after treatment.

Post-procedural DUS will assess the treatment efficacy [34]. Initial treatment success will be defined as complete target vein occlusion at 1 and/or 6 weeks. Anything else will be regarded as a technical failure. Recanalisation will be assessed at 52 weeks and is defined as blood flow within the target vein which has been treated. This will be broken down into partial < 25 % or full ≥ 25 % of the length of the treated vein. Residual disease is regarded as any reflux which was also present at baseline, but not a target for ablation. Disease progression will be defined as any reflux within a vein which was not present on baseline assessment. In the presence of clinical recurrence, DUS will be used to map out the pattern of the recurrence as this may give insight into techniques to avoid further recurrence and aid understanding of how recurrence comes about after these novel treatments. Post-procedural DUS will also look for evidence of complications such as heat-induced thrombosis, deep vein thrombosis, haematoma and superficial thrombophlebitis.

